#### Microbiological sampling and methods

Microbiological sampling and methods are performed as described [19]:

At inclusion, a lower respiratory tract sample used for the FAP *plus* and standard culture is obtained from all patients as soon as possible in the emergency department, either by induced sputum or by endotracheal aspiration. Depending on clinical symptoms, vital signs and medical history, sputum is induced either by nebulized isotonic (0.9%) or hypertonic (5.8%) saline. Patients with known obstructive lung disease and patients with hypoxemia or signs of airway obstruction upon physical examination are additionally treated with a bronchodilator (salbutamol and/or ipratropium bromide) prior to sampling. If sputum induction is unsuccessful, endotracheal aspiration is performed. Spontaneous sputum is accepted as an exception if an induced sputum or endotracheal aspiration cannot be collected

The standard methods include culture of respiratory tract samples and blood according to current guidelines (adapted from [20]). Blood culture isolates and relevant respiratory isolates are identified with matrix-assisted laser desorption/ionization time-of-flight mass spectrometry (MALDI-ToF MS) using Bruker’s microflex LT instrument, MBT Compass software ver. 4.1 and Compass Library DB-8468 (Bruker Daltonics, MA, USA). Nasopharyngeal and/or oropharyngeal swabs will be examined by an in-house real-time PCR test to detect respiratory viruses and atypical bacteria (influenza A and B, human parainfluenza viruses 1-3, respiratory syncytial virus, human metapneumovirus, rhinovirus, SARS-CoV-2, *Bordetella pertussis*, *Bordetella parapertussis*, *Mycoplasma pneumoniae* and *Chlamydia pneumoniae*). Standard methods also include the pneumococcal urine antigen test (Quidel Corporation, San Diego, USA). Any additional tests requested by the treating physician are also noted and counted as part of standard methods.

The representativeness of all sputum samples is evaluated by Gram staining (adapted from 22). Samples containing ≥ 10 squamous epithelial cells per field in at least 10 fields with 10× enlargement are considered non-representative. However, this criterion is disregarded if a significant amount of both leukocytes (≥ 10 times the amount of squamous epithelial cells per field of view) and a morphologically uniform microbe (> 5 microbes per field of view with 100× enlargement) are present. Samples are analysed by the FAP *plus* and cultured on agar plates, irrespective of their representativeness. Abundant growth of plausible respiratory pathogens is reported regardless of the representativeness of the sputum sample. Non-abundant growth is only considered in samples considered representative.

The FAP *plus* is an automated multiplex PCR test validated for lower respiratory tract samples. It is capable to detect 27 bacteria and viruses, as well as seven genetic markers of antibiotic resistance. The hands-on time is around 2 min and the total analysis time about 1 h [17]. Bacterial detections (except the atypical bacteria) are reported in a semi-quantitative manner and categorized as negative if ≤10^3.5^ copies/ml. Above this level, results are reported as positive and semi-quantitatively specified as 10^4^, 10^5^, 10^6^ or ≥ 10^7^ copies/ml [27].

#### Scoring systems and nutritional and physical status

Anthropometry, clinical scoring systems and physical tests are performed at the emergency department. Height, weight and body mass index (BMI) are registered and calculated. Physical capacity (muscle strength) is measured with a handgrip test adapted from [28]. Risk stratification of patients at admission is required to guide management and treatment decisions. The most established score systems (such as the CURB-65 score, Pneumonia Severity Index (PSI) and Sequential Organ Failure Assessment (SOFA) score) may accurately predict the severity and mortality in some CAP patients, but do not automatically identify patients that benefit from aggressive management strategies. We will register and evaluate several validated scoring systems: the CRB-65-score, CURB-65-score, SOFA-score, PSI-score, Charlton Comorbidity Index, Clinical Frailty scale, South African Triage Scale (SATS), Triage Early Warning Score (TEWS) and National Early Warning score 1 and 2 (NEWS 1 and 2). In addition, we will explore potential cognitive impairment at admission using the Abbreviated Mental Test 4 (4AT-score). Test calculators and form are available online [29–31].

Micronutrients important to immune function and CAP such as 25-OH vitamin D will be measured. Specifically, vitamin D regulates the production of antimicrobial peptides (cathelicidin and beta-defensin-2), which play an important role in the innate immune response to infection [32]. Data on habitual alcohol consumption and smoking will also be collected. Diabetes status will be assessed using HbA1c [33]. All participants will be tested at admission to identify unknown/new-onset diabetes and pre-diabetes, to differentiate admission hyperglycaemia between patients with and without diabetes (exhibit different risk profiles). We will assess acute dysregulation (the glycaemic gap) by comparing admission plasma glucose to estimated mean plasma glucose derived from HbA1c [34]. The cut-off values for both fasting and postprandial hyperglycaemia among the patients without diabetes will be defined by receiver operator curve analysis. In addition, we will record any other pre-admission comorbidities, such as chronic obstructive lung disease, heart disease and kidney disease.

#### Health economic data

Health economic data will be computed by combining information on molecular test performances, linked to consequences for costs for diagnosis and treatment. The Department of Microbiology, HUH, has developed a well-evaluated model for estimating the total cost of performing tests that includes reagents, technician time, instrument cost etc. This model will be used to calculate the actual cost of performing the FAP *plus*. The data collected will be used to conduct exploratory economic analyses and will include number and duration of medical care encounters, duration of hospitalization (total days or length of stay), number and type of diagnostic and therapeutic tests and procedures, potential cost reductions related to reduced hospital stay, reduced use of isolation rooms and possibly fewer days admitted to the intensive care unit and other factors like reduction in the use of antibiotics and more rapid transfer to per oral treatment will also be included.

#### Biobank

The respiratory tract samples will be frozen and stored in the biobank at HUH. Additional blood for transcriptional and immune marker profiling of patients (performed retrospectively) will be taken at admission and on day 3 of admission.

#### Biomarkers

Quantification of multiple proteins in selected clinical samples will be assessed by the Multiplex Bead Array-Bio-Plex assay (Bio-Rad Laboratories, Inc., CA, USA) using custom-designed human chemokine/cytokine kits and measured by the Bio-Plex 200 System (Bio-Rad Laboratories, Inc., CA, USA) with Luminex xMAP technology. For transcriptional profiling, we will target gene panels that include T and B cell markers as well as type 1 interferon-inducible genes. In addition, classifier genes that discriminate between viral and bacterial aetiology will be evaluated.

### Plans to promote participant retention and complete follow-up {18b}

The participants are included in the emergency department and the sampling of microbiological samples is done at the same time. We therefore do not need to promote participant retention.

### Data management {19}

Data will be entered into standardized patient-specific eCRFs provided by Viedoc, a commercial electronic clinical data entry system, which is used at HUH. All clinical and microbiological data entries (including range checks) are double-checked by study staff. The Viedoc application uses redundant enterprise-level storage area networks to store all data on separate data centres at separate geographic locations. In addition to the doubled data storage and application servers, a backup of all data is taken once every 2 h. Every 24 h, a copy of the latest backup is transferred to a third separate geographic location, and once a week, a copy of the backups is stored in a bank vault.

### Confidentiality {27}

Relevant data is entered into our study-specific eCRF created in the generic eCRF provided by Viedoc. Only designated and authorized personnel that are part of the study have access to the database. Participants are assigned a unique identifier. Any participant records or datasets that are transferred will contain the identifier only; participant names or any information which would make the participant identifiable are not transferred. The participants are required to give consent for their data to be used as described in the informed consent. For patients randomised to the FAP *plus* test, the results are made available in the patients’ electronic medical journal. The Department of Microbiology at HUH ensures the integrity and confidentiality of all microbiological data of enrolled patients by providing unique identification (ID) numbers for all person-identifiable data. All patient samples are assigned a unique sample ID (generated by the laboratory information system Unilab-700 (Alphasoft GmbH, Bochum, Germany)). Samples from patients enrolled in the CAPNOR study will be further assigned a CAPNOR study ID. At HUH, only authorized physicians employed at the Department of Microbiology or at the Department of Infectious Diseases have access to the UNILAB ID and to patient identifiable data.

### Plans for collection, laboratory evaluation and storage of biological specimens for genetic or molecular analysis in this trial/future use {33}

The respiratory tract samples collected at admission are frozen after analysis and stored at the Biobank at HUH. Plasma samples and PAXgene tubes collected at admission and at day 3 are also frozen and stored in the Biobank. Plasma and PAXgene tubes will be used for transcriptional and immune marker profiling.

## Statistical methods

### Statistical methods for primary and secondary outcomes {20a}

For the first primary outcome, which is a binary outcome capturing whether or not provision of pathogen-directed treatment was given, the comparison between arms will be performed using a logistic regression model. The difference between arms will be quantified by means of an odds ratio or as a difference in probabilities (“a risk difference”). For the second primary outcome, which is a quantitative outcome subject to right censoring capturing the time to pathogen-directed treatment was given, the comparison between arms will be carried out using a semi-parametric or fully parametric event-time model such as the Cox proportional hazards model or accelerated failure time model. Relevant covariate adjustment, including age and sex, will be included in both models.

Secondary outcomes will be analysed using the same two types of models as used for the two primary outcomes. However, for some quantitative secondary outcomes, there will be no right censoring present and, in such cases, linear models or linear mixed models will be fitted, depending on the absence or presence of repeated measurements.

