Tests using multiplex real-time polymerase chain reaction (PCR) can reduce the time to results compared with standard PCR panels from 12 to 48 h to about 2 h, with the potential to direct initial antimicrobial choice. The new generation BioFire® FilmArray® Pneumonia Panel *plus* (FAP *plus*) (bioMérieux S.A., Marcy-l’Etoile, France) includes the automated detection of 27 relevant bacterial (including atypical bacteria) and viral respiratory pathogens together with seven antimicrobial resistance genes [17]. The assay requires a 2-min hands-on time and a run time of about 1 h. We hypothesize that utilizing the FAP *plus* panel in CAP patients can improve both the time to and the proportion of patients receiving pathogen-directed treatment, thereby shortening the exposure to unnecessary antibiotics and the length of hospital admission.

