#### The standard-of-care arm

The comparator arm corresponds to standard-of-care diagnostics currently provided to CAP patients at HUH. As described [19], this includes bacterial culture of respiratory tract samples and blood according to current guidelines (adapted from [20]). Blood culture isolates and relevant respiratory isolates are identified with matrix-assisted laser desorption/ionization time-of-flight mass spectrometry (MALDI-ToF MS) using the Bruker’s microflex LT instrument, MBT Compass software ver. 4.1 and Compass Library DB-8468 (Bruker Daltonics, MA, USA). Nasopharyngeal and/or oropharyngeal swabs are examined by an in-house real-time PCR test to detect respiratory viruses and atypical bacteria (influenza A and B, human parainfluenza viruses 1-3, respiratory syncytial virus, human metapneumovirus, rhinovirus, SARS-CoV-2, *Bordetella pertussis*, *Bordetella parapertussis*, *Mycoplasma pneumoniae* and *Chlamydia pneumoniae*). The total turn-around time for the in-house PCR test is up to 48 h and is comparable to other centres nationally. Standard methods also include the pneumococcal urine antigen test (Quidel Corporation, San Diego, USA). Any additional tests requested by the treating physician are noted and counted as part of standard methods. A positive SARS-CoV-2 result, growth in blood cultures and positive pneumococcal antigen test results are phoned to the treating staff.

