#### *The FAP* plus *arm*

The FAP *plus* arm entails extended and rapid diagnostics on lower respiratory tract samples and telephonic feedback to treating staff with results. The feedback does not involve advice on treatment. All patients will receive the standard microbiological tests described above, with additional testing by the FAP *plus*. Through a feedback loop, both negative and positive FAP *plus* results are telephonically communicated to the treating staff.

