### Outcomes {12}

#### Primary outcomes

There are two primary outcome variables:Provision of pathogen-directed treatment based on a microbiological test result deemed as clinically relevant within 48 h of receipt of respiratory samples. This is a binary outcome variable taking on values as follows: yes, if such treatment was given to the patient, and no, if it was not given.Time (in hours) from receipt of respiratory samples to the patient receiving pathogen-directed treatment. This is a quantitative outcome variable recording the time elapsed from receipt of respiratory samples to provision of pathogen-directed treatment based on a microbiological test result deemed as clinically relevant (as defined in the first primary outcome) or an elapse of 48 h, whichever event came first. In other words, this outcome variable is subject to right censoring at 48 h. Right censoring could potentially occur for other reasons such as no aetiology being detected or the patient dying.

Since lack of microbiological identification is a major problem in CAP patients and enhancing rapid detection of significant pathogens could have a major impact on the clinical decision-making process, we selected two correlated primary outcomes with both time to and provision of pathogen-directed treatment. Limited evidence exists to support the use of these new molecular microbiological methods over standard of care, which uses standard microbiological testing. In a retrospective study including rapid molecular diagnostics, it has been suggested that de-escalation from broad-spectrum to pathogen-directed antibiotics could be undertaken in 77% of patients with CAP, while escalation should be done in 6%; however, a RCT is needed to confirm these findings [21].

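### Time to pathogen-directed treatment: a Cox test can miss a gain in speed when the 48-h proportions are similar; mean time restricted to 48 h fits the outcome and its sample size better

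*Protocol article*

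**What the plan says.** The second primary outcome is "Time (in hours) from receipt of respiratory samples to the patient receiving pathogen-directed treatment" (Primary outcomes). The same section says that "this outcome variable is subject to right censoring at 48 h", and adds that censoring may also occur because no aetiology was found or the patient died.

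Statistical methods {20a} assigns this outcome to a "semi-parametric or fully parametric event-time model such as the Cox proportional hazards model or accelerated failure time model", with covariates including age and sex. The final choice is left open.

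On timing, Background and rationale {6a} says that multiplex real-time PCR "can reduce the time to results compared with standard PCR panels from 12 to 48 h to about 2 h". The standard-of-care section says that the "total turn-around time for the in-house PCR test is up to 48 h", and that a positive SARS-CoV-2 result, "growth in blood cultures and positive pneumococcal antigen test results are phoned to the treating staff". The panel arm is not limited to the panel: "All patients will receive the standard microbiological tests described above".

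Sample size {14} sizes this outcome as a difference of 0.2 standard deviations in time, at significance level 0.025 and power 0.8, giving 477 per arm.

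**The concern.** The first primary outcome already tests the proportion treated within 48 h. The second earns its share of alpha by showing speed. With results at about 2 h in one arm and mostly at 12 to 48 h in the other, treatment changes prompted by the panel should fall early. Later events in the panel arm come from the standard tests and from patients not yet treated. The hazard ratio is then high at first and, where the 48-h proportions are similar, falls below 1. A Cox model averages these into one number whose size depends on how events are spread over the 48 h, and its test can have little power against a difference that is mostly one of timing.

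There is also a mismatch of scale. The outcome is defined in hours up to 48 h and was sized as a mean difference, whereas the named models naturally yield a hazard ratio or a time ratio.

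**Working it through.** **1. The plan's own figures.** A two-sided, two-sample t-test for 0.2 SD at alpha 0.025 and power 0.8 needs 476.5, so 477 per arm, as stated; 954/0.9 = 1060, as stated. For 50% versus 40%, the pooled two-proportion formula gives 470 per arm, and 940/0.9 = 1045, also as stated. So 477 per arm is a calculation for a difference in means, and a mean-based analysis needs no change in N.

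**2. Assumptions.** The protocol gives turnaround times but not event times, so these are assumed. Standard-test events are uniform over 12-48 h (mean 30, variance 108) and panel-prompted events uniform over 2-8 h (mean 5, variance 3). Untreated patients count as 48 h. There are 477 per arm; two-sided alpha 0.025 gives a critical value of 2.241.

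**3. One pattern by hand.** Take 40% treated by 48 h in both arms, with half of the panel arm's events early.
- Mean, panel arm: 0.2×5 + 0.2×30 + 0.6×48 = 35.8 h. Mean, standard arm: 0.4×30 + 0.6×48 = 40.8 h. Difference 5.0 h.
- Variance, panel arm: 0.2×28 + 0.2×1008 + 0.6×2304 − 35.8² = 308.0. Variance, standard arm: 0.4×1008 + 0.6×2304 − 40.8² = 121.0. Average SD = √214.5 = 14.6 h.
- SE = √((308.0 + 121.0)/477) = 0.948 h; z = 5.0/0.948 = 5.27; power = Φ(5.27 − 2.24) = 99.9%.
- Hazard ratio after 12 h: in the panel arm 80% are still untreated and a quarter of them (0.20/0.80) have the event; in the standard arm 40% do. ln(0.75)/ln(0.60) = 0.56. Before 12 h only the panel arm has events. The hazards are not proportional.
- Simulated overall Cox hazard ratio: 1.13, with power 14-15%.

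**4. Other patterns, simulated power (600 to 1,500 runs each; Monte Carlo error up to about 2 points):**

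| Treated by 48 h, panel vs standard | Timing in panel arm | Cox | Restricted mean |
|---|---|---|---|
| 40% vs 40% | all events at 2-8 h | 57-61% | 100% |
| 40% vs 40% | all events at 2-24 h | 42% | 100% |
| 40% vs 40% | 10% of patients in each arm treated early by shared rapid tests; other panel-arm events at 2-8 h | 34% | 100% |
| 40% vs 40% | half of events early | 14-15% | over 99% |
| 40% vs 40% | the same shared 10%; other panel-arm events half early, half late | 9% | 85-89% |
| 45% vs 40% | half early | 73-76% | 100% |
| 50% vs 40% | half or all early | 99-100% | 100% |
| 50% vs 40% | one tenth of events early | 87% | 95% |
| 50% vs 40% | no speed gain | 77-82% | 56-60% |

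The last row checks by hand: difference 40.8 − 39.0 = 1.8 h; SE = √((135.0 + 121.0)/477) = 0.733; z = 2.46; power = Φ(0.22), about 59%.

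**5. Dependence on the event rate.** With half of the panel arm's events early and equal proportions in both arms, Cox power is about 32% at 50%, 61% at 60%, 86% at 70% and 99% at 80%.

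**6. Accelerated failure time models.** Over the five 40% versus 40% patterns (150 runs each, error about 4 points), power is 17-68% for Weibull, 44-100% for log-logistic and 65-100% for log-normal. Log-normal keeps 99-100% in all but the fifth pattern.

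**The case against.** **Only a class of models is named, with examples.** That class includes models from which a mean in hours can be derived, and an analysis plan that is not shown may settle the choice. This stands, and the open choice alone would be no finding. What remains is visible in the protocol: the models it puts forward do not match the mean-difference scale of its own sample size, and its own turnaround times argue against proportional hazards.

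**A reader might infer that accelerated failure time models fail too.** The protocol does not support that. Rescaling 12-48 h to 1-4 h is constant acceleration, and the log-normal family largely kept its power.

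**A reader might infer that 50-60% of patients are expected never to have the event.** The 50% and 40% in Sample size {14} are expected rates of pathogen identification. Section {18a} also counts stopping treatment on negative results, and negative panel results are phoned, so event rates may be higher. Step 5 shows that the Cox loss then shrinks.

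**A reader might suspect a data-driven model choice because the statisticians are not blinded.** The blinding section adds that they have no direct access to the data.

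**Equal 48-h proportions are not the trial's hypothesis.** True: at the planned 50% versus 40% with a substantial speed gain, Cox misses nothing, and with no speed gain it is the stronger test.

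**The 12-48 h figure covers PCR panels only.** Other results are phoned in both arms, and clinicians' time to act is not given. Allowing for shared rapid tests does not rescue Cox, however: its power is 34% and 9% in those patterns.

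**Conclusion.** The point holds in limited form. Proportional hazards is implausible under the protocol's own turnaround times, and a Cox test can miss a gain in speed when the 48-h proportions are similar: about 9-60% power at 40% versus 40%, against 85-100% for the restricted mean. The loss is not general. At 50% versus 40% Cox has 99-100% power if at least half of the panel arm's events are early, and 87% (against 95%) if only a tenth are. Cox is ahead in the 50% versus 40% case with no speed gain.

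The powers rest on assumed event-time shapes and 48-h event rates; the failure of proportionality needs only the turnaround times and mostly early action on panel results. Whether an accelerated failure time analysis suffers depends on the family chosen. This is an improvement that should be made before analysis, not an error that invalidates the design.

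**What to change.** **Statistical methods {20a}.** Make the primary analysis of the second primary outcome the age- and sex-adjusted difference between arms in mean time restricted to 48 h. Use a linear model for the smaller of event time and 48 h with robust standard errors, or restricted-mean regression if a few patients are censored by withdrawal. Report it in hours with cumulative incidence curves, and keep the Cox hazard ratio as a secondary summary.

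**Primary outcomes.** Do not censor patients early because no aetiology was found, since such censoring is informative and would bias the restricted mean as well. Count patients without pathogen-directed treatment as 48 h, and state how deaths before 48 h enter the analysis.

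**Sample size {14}.** N need not change. The 3- and 5-day SD examples should go: a time confined to 0-48 h has an SD of at most 24 h, so 0.2 SD is at most 4.8 h.

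**Cost.** Analysis-plan wording and simple code. The hazard ratio is no longer the headline figure. Power falls to about 59%, against 79% for Cox, if the panel raises the 48-h proportion from 40% to 50% with no gain in speed, an effect that the first primary outcome already tests.
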